### Adverse Event Reporting and Monitoring

All adverse events (AEs) will be documented at each follow-up. Serious AEs will be reported to the Institutional Ethics Committee within 7 days and nonserious AEs within 30 days. A data monitoring committee comprising 2 ophthalmologists and 1 biostatistician will perform quarterly reviews of safety, recruitment progress, and protocol compliance. Any protocol amendments will require prior institutional ethics committee approval and updating of the Clinical Trial Registry of India.

### Data Management and Statistical Analysis

Statistical methods used for data management and analysis are summarized in this section. Continuous variables (eg, BCVA, astigmatism, and intraocular pressure) will be summarized as mean (SD) and analyzed using the independent *t* test for between-group comparisons and repeated-measures ANOVA for longitudinal analysis. Categorical variables (eg, complications and sex) will be compared using the chi-square test or the Fisher exact test. Multivariate analysis will be performed using mixed-effects linear regression to adjust for baseline covariates (age and preoperative vision). Missing data will be handled using multiple imputation under a missing-at-random assumption. Interim analysis will be conducted after 50% enrollment to evaluate safety and adherence; no stopping rules for efficacy are planned. Statistical analyses will be performed using SPSS software (version 27.0; IBM Corp). A *P* value <.05 will be considered statistically significant.

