**Methods:**

This is a prospective, 2-arm, open-label randomized controlled trial being conducted at the Department of Ophthalmology, Acharya Vinoba Bhave Rural Hospital, Sawangi, India. A total of 92 patients aged 35 to 75 years with intraoperative posterior capsular compromise will be randomized (block randomization, sealed opaque envelopes) into 2 groups: group A (retropupillary iris-claw IOL) and group B (scleral-sutured IOL). Preoperative, intraoperative, and postoperative data will be collected at day 1, day 15, day 30, and day 90. The primary outcomes are best-corrected visual acuity and lens-induced astigmatism at 3 months. Secondary outcomes include IOL centration or tilt, intraoperative and postoperative complications, and patient satisfaction (assessed using the National Eye Institute Visual Function Questionnaire-25). Data will be analyzed using ANOVA and mixed-effects models.

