### Outcome Measures

Primary outcomes:

BCVA at 3 months using Snellen’s chart, converted to logMAR values for statistical analysis.Lens-induced astigmatism, measured through keratometry and autorefractometry.

Secondary outcomes:

Intraoperative complications (posterior capsular rupture extension, vitreous loss, surgical duration).Postoperative complications (hyphema, pigment dispersion, raised intraocular pressure, IOL decentration, cystoid macular edema).IOL centration and tilt, assessed by slit-lamp retroillumination following the method of Calzetti et al [10].Patient-reported satisfaction and visual function, measured using the National Eye Institute Visual Function Questionnaire-25 at 3 months.

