This trial’s methodological design addresses previous limitations by incorporating randomization, allocation concealment, and masked outcome assessment. Objective parameters such as IOL tilt and decentration will be evaluated using slit-lamp retroillumination and validated anterior-segment optical coherence tomography methods described by Calzetti et al [10], ensuring quantitative reproducibility. In addition, the inclusion of patient-reported outcomes using the National Eye Institute Visual Function Questionnaire-25 will provide valuable insights into subjective satisfaction and functional vision, which have often been underrepresented in earlier studies.

Ethical oversight, AE monitoring, and quarterly data review by an independent committee have been included to maintain methodological rigor and compliance with Good Clinical Practice guidelines. The statistical plan using mixed-effects modeling and repeated-measures ANOVA will allow robust analysis of longitudinal data while accounting for missing values. The trial does not include an economic analysis, as cost-effectiveness was beyond the scope of the present protocol; however, results regarding operative time and complication rates may have indirect implications for resource optimization in tertiary-care settings. Potential limitations of this study include its single-center design and limited sample size, which may influence external generalizability. Nonetheless, the use of standardized surgical techniques, strict eligibility criteria, and a uniform postoperative evaluation schedule are expected to enhance internal validity and reproducibility.

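### Two primary outcomes are each judged at an unadjusted P<.05, with no rule on whether one or both must succeed and no statement of which of three analyses decides the 3-month result

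*Protocol article*

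**What the plan says.** The Methods paragraph of the Abstract states: "The primary outcomes are best-corrected visual acuity and lens-induced astigmatism at 3 months". Outcome Measures lists the same two, the second as "Lens-induced astigmatism, measured through keratometry and autorefractometry".

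Data Management and Statistical Analysis gives BCVA and astigmatism as examples of continuous variables. It assigns such variables to an independent *t* "test for between-group comparisons and repeated-measures ANOVA for longitudinal analysis", and then adds: "Multivariate analysis will be performed using mixed-effects linear regression to adjust for baseline covariates", the covariates being age and preoperative vision. One threshold covers everything: a P "value <.05 will be considered statistically significant".

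Elsewhere the list of methods is shorter. The Abstract says "Data will be analyzed using ANOVA and mixed-effects models". The Discussion says that "mixed-effects modeling and repeated-measures ANOVA will allow robust analysis of longitudinal data while accounting for missing values". Neither mentions the *t* test.

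No section calls one analysis primary, orders the two outcomes, divides the significance level between them, or says whether one or both must succeed. The Hypothesis section names both outcomes in a single claim of noninferiority or superiority and gives no decision rule.

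**The concern.** With two primary outcomes and no rule linking them, a significant result on either could be reported as a positive trial. With three methods and none designated, each outcome may also yield more than one P value for the group effect.

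The methods do not estimate the same quantity. The *t* test at Day 90 compares arms at the stated endpoint. The between-group term of a repeated-measures ANOVA averages over visits. According to Table 1 these are Days 15, 30 and 90 for BCVA, but only Days 15 and 90 for astigmatism. The mixed model can give a Day-90 contrast or an average over visits, depending on how it is written.

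At stake is whether a reader of the results can tell which P value was meant to settle the primary question, and what false-positive risk goes with it.

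**Working it through.** **Inputs from the document.** Two primary outcomes; P<.05 per test (two-sided assumed, as sidedness is not stated); 92 patients allocated 1:1, so 92/2 = 46 per arm. No efficacy stopping is planned at the interim analysis, so nothing is added for it. The document states no familywise error rate, so there is no figure of its own to reproduce beyond the per-test .05.

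**Assumed, not in the document.** All correlations: between outcomes, between visits, and between preoperative vision and BCVA.

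**Step 1: one test per outcome, no true difference on either.**

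- Independent outcomes: 1 − (1 − 0.05)² = 1 − 0.9025 = 0.0975.
- Correlated outcomes: 1 − P(|Z₁| < 1.96 and |Z₂| < 1.96) under a bivariate normal distribution.

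| Correlation of the two test statistics | Chance of at least one P<.05 |
|---|---|
| 0 | 9.75% |
| 0.3 | 9.5% |
| 0.5 | 9.1% |
| 0.7 | 8.4% |
| 0.9 | 7.0% |

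The range is about 7% to 10%.

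**Step 2: choice among group-effect analyses left open.** Null simulation with 46 per arm and 6,000 trials in each of six scenarios. Correlation between visits was 0.5 to 0.9, preoperative vision with BCVA 0.3 to 0.5, and between the outcomes' patient-level effects 0 to 0.7. Each outcome was given three visits as a simplification. A Day-90 regression adjusted for the preoperative value stood in for the mixed model.

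| Tests allowed per outcome | At least one P<.05, two outcomes |
|---|---|
| *t* test only | 8.6% to 9.9% |
| *t* test or adjusted Day-90 regression | 10.5% to 12.6% |
| *t* test or ANOVA group effect | 10.4% to 15.2% |
| Any of the three | 12.0% to 16.8% |

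The Monte Carlo standard error is at most about √(0.17 × 0.83 / 6000) = 0.5 percentage points. A separate simulation with independent outcomes put the two Day-90 analyses at 11% to 14%. Another, using Table 1's actual visits (three for BCVA, two for astigmatism), gave 15% to 16% for any of the three. About 11% to 17% summarises these results. Six fully independent tests would give 1 − 0.95⁶ = 26.5%, which overstates the risk because the methods share the same data.

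**Step 3: one outcome alone.** Choosing among the three group-effect analyses gives 7.8% to 9.8% for BCVA. A both-must-succeed rule would therefore remove the inflation from having two outcomes, but not the inflation from open choice of method.

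**Step 4: after the fix.** With one analysis per outcome and a fixed sequence, a false claim when neither outcome differs requires BCVA to reach P<.05, so the rate is at most 5%. If BCVA truly differs, astigmatism is tested once at .05, again at most 5%. If both must be significant, the rate is also at most 5%.

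**The case against.** The strongest defence is that the statistical section already gives each method its own role: the *t* test for comparing groups, ANOVA for the time course, and the mixed model for covariate adjustment. The Hypothesis section can also be read as requiring both outcomes, in which case having two adds no inflation. An article condenses its source, and a separate analysis plan may name the deciding model.

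Part of this stands. The roles are a reason not to treat the ANOVA group-by-time term as a primary result. They do not settle whether the unadjusted or the adjusted comparison decides Day 90, and the Abstract and Discussion omit the one method that the Methods section assigns to between-group comparison. The two-outcome reading of the Hypothesis is possible but nowhere stated. The article itself fixes the methods and the threshold, so this is more than detail left for later.

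Three stronger readings are tempting and are not supported:

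- **A false-positive risk near 25%.** Adding the group-by-time test gives 20.2% to 23.9% in the same simulation. That counts a test of trajectory as a 3-month primary result, although the section assigns ANOVA to longitudinal analysis.
- **That repeated-measures ANOVA will discard patients with a missed visit, making the Discussion wrong.** The statistical section plans multiple imputation under a missing-at-random assumption. The Discussion sentence also credits the mixed model and ANOVA together.
- **That the article promises a 5% familywise rate and breaks it.** It states only a per-test threshold.

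The figures also concern tests of difference. They do not describe the error rate of a noninferiority claim, which the Hypothesis also contemplates.

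**Conclusion.** The point holds in limited form. The plan has two primary outcomes, three named methods, a single unadjusted .05, no deciding analysis and no one-or-both rule. The false-positive risk across the primary outcomes is about 7% to 10% with one test each, and about 11% to 17% if any group-effect analysis may be chosen.

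The structural facts come straight from the text. The percentages depend on assumed correlations, two-sided tests of difference, no true difference on either outcome, and a regression standing in for the mixed model. A stated requirement that both outcomes succeed would remove the part due to having two outcomes. The ambiguity is worth settling now: the Results section says that no interim data have been analyzed, and a choice made after seeing the results would not protect the primary conclusion.

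**What to change.** Make these changes before any comparison of outcomes between arms is seen.

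1. Name one deciding analysis for each primary outcome: the Day-90 arm contrast from the mixed model already planned, adjusted for age and preoperative vision, with arm-by-visit terms so that Day 90 can be isolated. Table 1 lists no preoperative counterpart of lens-induced astigmatism, so the planned covariates suffice there.
2. Label the *t* test and repeated-measures ANOVA as supportive.
3. State the rule for two outcomes: either a fixed sequence at .05 (BCVA first, astigmatism only if BCVA is significant), or a requirement that both be significant. If the claim is to be noninferiority, define success at the first step in those terms.
4. Make the Abstract, Data Management and Statistical Analysis, and the Discussion agree.

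**Cost.** Only wording changes, and the number of patients stays the same. Under the fixed sequence, astigmatism cannot be claimed as a confirmatory result if BCVA fails. Under the both-must-succeed rule, power is lower than for either outcome alone.

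Splitting the level at .025 each would also work (1 − 0.975² = 4.94% if independent) but costs more. If power were 80% at .05 (an assumption, since the sample size appendix is not shown), it would fall to Φ(2.802 − 2.241) ≈ 71%. Restoring it would need (3.083/2.802)² ≈ 1.21 times as many patients, or about 112 instead of 92. Holm's procedure has a similar entry cost, because it tests the smaller P value at .025.

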### Randomization, Allocation Concealment, and Blinding

Eligible patients will be randomly allocated in a 1:1 ratio into 2 groups: group A (retropupillary iris-claw IOL) and group B (scleral-sutured fixation). A computer-generated block randomization sequence (block size of 4) will be prepared by an independent statistician. The group assignment will be concealed in sequentially numbered, opaque, sealed envelopes opened only after capsular deficiency confirmation during surgery.

Due to the nature of the interventions, blinding of surgeons and patients will not be feasible. However, postoperative outcome assessors and data analysts will remain blinded to the intervention group to minimize observer bias. Postoperative assessors will follow standardized grading protocols and will remain masked to group assignment to reduce detection bias.

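### No single analysis is designated for BCVA at 3 months: an unadjusted t test, a repeated-measures ANOVA and an adjusted mixed model share one P<.05, and the abstract omits the t test

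*Protocol article*

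**What the plan says.** Under Outcome Measures, the first primary outcome is "BCVA at 3 months using Snellen’s chart, converted to logMAR values for statistical analysis". Table 1 schedules BCVA at Days 15, 30 and 90.

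The Data Management and Statistical Analysis section names BCVA among its continuous variables and gives it the independent t "test for between-group comparisons and repeated-measures ANOVA for longitudinal analysis". It goes on: "Multivariate analysis will be performed using mixed-effects linear regression to adjust for baseline covariates (age and preoperative vision"). A P "value <.05 will be considered statistically significant", with no distinction between methods. No analysis is called primary or supportive.

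The abstract's Methods paragraph says "Data will be analyzed using ANOVA and mixed-effects models" and does not mention the t test.

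**The concern.** Someone who reads only the abstract would expect ANOVA and mixed models to decide the 3-month comparison. Someone who reads the analysis section would expect the t test, because that is the method attached there to comparing the arms. These methods can give different answers on the same data, and nothing in the article says which one counts.

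Two things are at stake. First, the 5% error rate for the BCVA comparison is not protected, because the deciding test could be settled after the results are seen. Second, the ANOVA group effect concerns the average over three visits. A difference in early recovery that has gone by Day 90 could appear as an overall group effect, and a difference present only at Day 90 could be diluted.

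There is also a missed gain. The one stated between-group comparison is unadjusted, although the trial records preoperative vision and age and already plans to adjust for them elsewhere.

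**Working it through.** **Inputs from the protocol.** "A total of 92 patients aged 35 to 75 years with intraoperative posterior capsular compromise will be randomized" (abstract), and "Eligible patients will be randomly allocated in a 1:1 ratio into 2 groups" (Randomization section), so 92/2 = 46 per arm. Threshold 0.05, taken as two-sided because the sidedness is not stated. BCVA visits: Days 15, 30 and 90. The sample size of 92 cannot be reproduced, since its inputs are in an appendix that is not shown; nothing below depends on how it was derived.

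**Assumed, not in the documents.** Equal SD at each visit, equal correlation ρ between visits (0.5 to 0.8), correlation of preoperative vision with the outcome mostly 0.3 to 0.5, complete data.

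**1. What each method estimates**
- t test at Day 90: the Day 90 mean difference.
- ANOVA group effect: the mean of the Day 15, 30 and 90 differences. The group-by-time test concerns the shape of recovery.
- Mixed model adjusted for age and preoperative vision: the Day 90 difference if it has an arm-by-visit term and that contrast is read; a visit-averaged difference if it has a single arm effect. The text does not say which.

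A different target is therefore shown for the ANOVA only.

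**2. Error rate if any significant result could be claimed.** Null data were simulated with 46 per arm and three visits. Independent runs of 8,000 to 20,000 trials per setting agreed:
- Each test alone: 4.5% to 5.4%.
- At least one of the t test, ANOVA group effect and adjusted group effect: 7.8% to 9.4%, that is about 8% to 9%. If the mixed model reads the Day 90 contrast instead: 8.7% to 9.4%.
- Adding the group-by-time test: 11.6% to 13.5%, that is about 12% to 13%.

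Some runs also covered ρ down to 0.3 and up to 0.9, with baseline correlations from 0 to 0.6; their results lie within these ranges. Three independent tests would give 1 − 0.95³ = 14.3%; the figures are lower because the tests are correlated.

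**3. How far the ANOVA group effect can depart from Day 90.** For a visit mean, SD = √((1+2ρ)/3) in units of the single-visit SD. With mean difference m, the standardized effect is m/SD and the noncentrality is (m/SD)·√(46/2), on 90 degrees of freedom.
- Arms differ by 0.6 SD at Days 15 and 30 and by nothing at Day 90: m = (0.6+0.6+0)/3 = 0.4. At ρ = 0.5, SD = 0.816, noncentrality = 0.490 × 4.796 = 2.35, and the ANOVA group effect is significant 64% of the time. At ρ = 0.7 it is 56%; at 0.8, 53%.
- Arms differ by 0.6 SD at Day 90 only: m = 0.2, and ANOVA power is 21%, 19% and 17% at ρ = 0.5, 0.7 and 0.8. The Day 90 t test has noncentrality 0.6 × 4.796 = 2.88 and power 81%.

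**4. Gain from adjustment.** Variance is multiplied by 1 − r². For r = 0.3 the reduction is 0.09 (9%); for r = 0.5 it is 0.25 (25%).

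**The case against.** The strongest reply is that the analysis section gives the methods distinct roles: the t test for comparing arms, the ANOVA for the time course, the mixed model for adjustment. With the primary time point fixed at 3 months, the natural reading is a Day 90 t test, which is valid in a randomized trial. The abstract's two methods both appear in the analysis section, so its list is a subset rather than a rival plan. This is also a condensed article, and model terms may sit in an analysis plan that is not shown.

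Much of this stands, and it rules out several stronger readings:
- A reader might infer that the 5% error rate is already lost. It is not. No passage says that any significant result will count, and each test alone holds about 5%.
- A reader might infer that all three methods estimate different quantities. A mixed model with a Day 90 contrast targets the same mean difference as the t test.
- A reader might count the Discussion as a second conflict, because it speaks of "The statistical plan using mixed-effects modeling and repeated-measures ANOVA" without the t test. That sentence is about longitudinal data only, so leaving out a single-time-point test contradicts nothing.
- The scenarios in step 3 are not false positives in themselves. An early difference would be real; it misleads only if reported as a 3-month result, which the protocol does not propose.

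What the reply does not remove is that no analysis is designated, that one threshold serves all, and that the abstract drops the only method assigned to comparing the arms. The missing arm-by-visit term alone would be a detail for an analysis plan; it matters here only because the deciding analysis is not named.

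**Conclusion.** The point holds as a gap in designation together with an omission in the abstract. It is not a demonstrated loss of error control. The 3-month BCVA comparison has three candidate analyses at P<.05, and one of them, the ANOVA group effect, does not estimate the Day 90 difference. The possible inflation, to about 8% to 9% or to 12% to 13% with group-by-time, is conditional on choosing among the results and rests on assumed correlations. Naming one adjusted Day 90 contrast gives a single test at the stated primary time point, and 9% to 25% lower variance if the assumed baseline correlation of 0.3 to 0.5 applies. Preferring the adjusted model to the valid unadjusted t test is an improvement in precision, not the correction of an error. The point should be acted on because it costs so little and because the Results section reports that no interim data have been analyzed.

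**What to change.** In the Data Management and Statistical Analysis section:
- Name one primary analysis of BCVA: the Day 90 difference between arms in logMAR, with 95% CI, from a mixed model with arm, visit, arm-by-visit, age and preoperative vision.
- For lens-induced astigmatism, name covariate-adjusted linear regression at Day 90.
- Label the unadjusted t test supportive.
- Use the repeated-measures ANOVA only to describe recovery over time, and do not offer its group effect as evidence on the 3-month outcome.

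Align the abstract's sentence on analysis with this. The Discussion sentence needs no correction on this account.

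The cost is wording only: the data, visits, covariates and software stay as planned. The one downside is that a supportive analysis could no longer be quoted as confirming the primary outcome.

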### Timeline of Assessments

The schedule of preoperative, intraoperative, and postoperative assessments is outlined in Table 1.

**Table 1. T1:** Timeline of clinical assessments and outcome measures.

Study phase	Assessment parameters
Preoperative	Visual acuity (Snellen’s chart), slit-lamp biomicroscopy, intraocular pressure (NCT^a^), fundus evaluation, and biometry (A-scan, keratometry)
Day 0 (surgery)	Type of IOL^b^ fixation, intraoperative complications, surgical duration, and intraoperative stability
Day 1	Corneal clarity, anterior chamber reaction, intraocular pressure, and early complications
Day 15	BCVA^c^, astigmatism (autorefractometry), anterior chamber reaction, and IOL position
Day 30	BCVA, lens centration/tilt (slit-lamp retroillumination as per Calzetti et al [10]), intraocular pressure, and patient comfort
Day 90	Final BCVA, lens-induced astigmatism, postoperative complications, and patient satisfaction (NEI VFQ-25^d^)

a NCT: noncontact tonometry.

b IOL: intraocular lens.

c BCVA: best-corrected visual acuity.

d NEI VFQ-25: National Eye Institute Visual Function Questionnaire-25.

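### The adjusted model names only age and preoperative vision as covariates; using the preoperative pressure and keratometry already collected would be a free, minor gain in precision for pressure and possibly for astigmatism.

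*Protocol article*

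**What the plan says.** All references are to the protocol article.

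- **Data Management and Statistical Analysis** opens with "Continuous variables (eg, BCVA, astigmatism, and intraocular pressure) will be summarized as mean (SD") and has them "analyzed using the independent *t* test for between-group comparisons and repeated-measures ANOVA for longitudinal analysis". A later sentence adds "mixed-effects linear regression to adjust for baseline covariates (age and preoperative vision"). No further covariate is named, and the sentence does not say which outcomes the model covers.
- **Timeline of Assessments, Table 1**, preoperative row, lists visual acuity and also "intraocular pressure (NCT^a^), fundus evaluation, and biometry (A-scan, keratometry"). After surgery, pressure is listed at day 1 and day 30, astigmatism by autorefractometry at day 15, and lens-induced astigmatism at day 90.
- **Outcome Measures** has two primary outcomes. BCVA at 3 months is "converted to logMAR values for statistical analysis". The other is "Lens-induced astigmatism, measured through keratometry and autorefractometry", with no statement of how the value is derived. Among the secondary outcomes, pressure appears only within "Postoperative complications (hyphema, pigment dispersion, raised intraocular pressure, IOL decentration, cystoid macular edema").

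**The concern.** A baseline covariate earns its place by predicting the outcome. Preoperative vision does that job for BCVA, since it is the same quantity measured earlier. It has little reason to predict postoperative pressure or cylinder, because in these eyes it is lowered by the cataract that surgery removes. The measurements that would be expected to predict those two outcomes are taken before surgery in every patient, and no named analysis uses them as covariates.

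What is at stake is the width of the confidence intervals for pressure, which bears on safety, and possibly for lens-induced astigmatism, which is a primary outcome. The Discussion itself lists limited sample size as a limitation, so precision that costs nothing is worth taking.

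**Working it through.** **Is there a figure of the plan's own to reproduce?** No. The document gives no correlation, standard deviation or effect size, and refers the sample size calculation to an appendix that is not shown. The total of 92 therefore cannot be rebuilt from the text at hand. That is no fault of the plan, and this point does not depend on it.

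**Inputs.** N = 92 (Abstract), allocated 1:1 (Randomization section), so 46 per arm. Significance level 0.05 (Data Management and Statistical Analysis), taken as two-sided, which is an assumption. The correlation r between the outcome and the added baseline, beyond what age and preoperative vision explain, is also an assumption, shown over a range.

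**Precision.** Residual variance after adding the baseline is (1 − r²) times its value without it. The standard error is multiplied by √(1 − r²), and the equivalent sample size is 92/(1 − r²). For scale, 46 per arm gives 80% power for a difference of (1.960 + 0.842) × √(2/46) = 0.584 SD. The last column gives power for that same difference, by the normal approximation Φ(0.584/[√(1 − r²) × √(2/46)] − 1.960), with no dropout.

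| assumed r | variance removed | SE multiplier | equivalent N | power at 0.584 SD |
|---|---|---|---|---|
| 0 | 0% | 1.000 | 92 | 80.0% |
| 0.1 | 1% | 0.995 | 92/0.99 = 93 | 80.4% |
| 0.3 | 9% | 0.954 | 92/0.91 = 101 | 83.5% |
| 0.5 | 25% | 0.866 | 92/0.75 = 123 | 89.9% |

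The gain is negligible at r = 0.1 and useful from about 0.3 upwards.

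**Chance imbalance.** The standard error of the between-arm difference in a baseline is √(2/46) = 0.21 SD. An imbalance of that size moves the unadjusted outcome difference by r × 0.21 SD: about 0.02, 0.06 and 0.10 SD at r = 0.1, 0.3 and 0.5. The unadjusted standard error already allows for this, so it is not bias.

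**Which outcomes gain.**
- *BCVA:* nothing to add; its own baseline is already in the model.
- *Pressure as a continuous measure:* preoperative pressure is the same quantity measured earlier, so the table applies directly.
- *Lens-induced astigmatism:* astigmatism due to the new lens has no preoperative value. Keratometric cylinder is a related covariate, not the outcome's own baseline, and the gain depends on the derivation.
  - If the outcome is refractive minus corneal cylinder at the same visit, the corneal part is already removed and the further gain may be small.
  - If it is a change from preoperative cylinder, then with equal variances the change score has variance 2(1 − r) against 1 − r² after adjustment, r here being the correlation of the two readings. At r = 0.5 this is 1.00 against 0.75. The proportion saved is (1 − r)/2, so it shrinks as the two readings agree more closely: at r = 0.9 it is 0.20 against 0.19, a saving of 5%.

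**The case against.** The strongest case against has four parts.

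1. The sentence on the mixed-effects model does not say which outcomes it covers. BCVA, astigmatism and pressure are examples in an earlier sentence about t tests and repeated-measures ANOVA, and a model adjusting for preoperative vision may be meant for BCVA alone. This stands as far as it goes: a reader might infer that one covariate set is fixed for every continuous outcome, but the text does not say so. Under the narrower reading, however, astigmatism and pressure have no covariate-adjusted analysis at all, so naming their baselines would still help.
2. A condensed article may leave covariate lists to an analysis plan. That would answer a complaint about silence. Here the article states a covariate list, and the point is that the stated list suits one of the three measures it names.
3. Pressure is listed as an outcome only in the form of a complication, and complications go to chi-square or Fisher exact tests, where a linear-model covariate plays no part. It is also not stated whether the preoperative reading enters the repeated-measures ANOVA as a time point. This stands, and it confines the gain to pressure analysed as a continuous measure.
4. The between-group comparison is assigned to the unadjusted t test, which is valid under randomization and which a change of covariates in a separate model does not touch. This stands, and it is why the fix must also say that the adjusted estimates are reported.

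Two stronger readings are tempting. A reader might infer that no outcome is adjusted for its own baseline; that is false for BCVA. A reader might also infer that the trial is losing the equivalent of a definite number of patients on a primary outcome. The document gives no correlation, and for lens-induced astigmatism no loss is demonstrated.

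**Conclusion.** The point holds as a free improvement of minor severity. The only covariates named are age and preoperative vision. They suit BCVA but are a poor choice for pressure and astigmatism, although better-matched baselines are already collected, and no other part of the document brings those baselines in as covariates.

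The loss is one of precision: r² of the residual variance, or about 1%, 9% and 25% at assumed partial correlations of 0.1, 0.3 and 0.5. It is clearest for continuous pressure, a safety measure. For lens-induced astigmatism it is conditional on a derivation that the document does not give, and may be small. Nothing here makes the planned analysis invalid or biased.

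**What to change.** In Data Management and Statistical Analysis, replace the single covariate list with an outcome-specific one: preoperative vision for BCVA, preoperative keratometric cylinder for astigmatism, preoperative intraocular pressure for pressure, with age in all three. State that these adjusted between-group estimates will be reported alongside the unadjusted t tests. Cylinder should enter in the form that matches the outcome (as vector components if the outcome is analysed that way).

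The cost is a sentence or two of analysis text, with no new measurement, visit or patient. Under the article's own rule on amendments, it also needs ethics committee approval and a registry update. The Results section reports that no interim data had been analysed at submission. If that is still so, the choice can be fixed before anyone has seen outcome comparisons.
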